#### Daily caloric restriction (DCR) group

Participants in this group will be given a calorie goal designed to produce a 34% energy deficit from baseline estimated individual weight maintenance energy requirements for the duration of the 52-week intervention. As in the IMF group, weight maintenance energy requirements will be determined as (measured REE × activity factor of 1.5) [35]. Participants will be guided to target diet macronutrient content of 55% carbohydrates, 15% protein, and 30% fat.

#### PA prescription

Participants in both groups will also receive a recommendation to gradually increase moderate intensity PA to 300 min/week over the initial 26 weeks and to maintain this level of PA for the duration of the study (see Table 1 for ramp-up). This target is consistent with current PA guidelines for weight management [34, 43]. Participants will be instructed in how to use a relative intensity scale [34] to achieve the target of moderate intensity.

**Table 1 Tab1:** Description of timeline for PA ramp-up

Study Week	Days/week	Session duration (min/day)	Total duration (min/week)
0	Establish fitness center membership, orientation		
1	3	20	60
2	3	25	75
3–4	3	30	90
5–6	3	35	105
7–8	3	40	120
9–10	3	45	135
11–12	3	50	150
13–14	3	60	180
15–20	4	60	240
21–52	5	60	300

*PA* Physical activity

#### Strategies to improve adherence to interventions {11c}

#### Group-based behavioral support

To improve adherence to the interventions, both groups will receive a 52-week group-based behavioral weight loss program with equivalent contact and support (see Table 2 for a list of weekly behavioral support topics). The programs will fulfill all recommendations for behavioral interventions for treatment of obesity outlined in current guidelines [17]. Randomized groups will meet separately. Curriculum for DCR will be based on the Colorado Weigh behavioral weight loss program which was developed at CU-AMC in 2000 and uses a skills-based approach and cognitive behavioral strategies for lifestyle modification with a dietary focus on DCR [44, 45]. Curriculum for IMF will also be based on the Colorado Weigh behavioral weight loss program and features similar weekly curriculum themes as used in DCR but adapted by the study PI (VC) with input from a registered dietitian (KB) and a behavioral psychologist (AC) to focus on behavioral support specific to IMF. Group meetings will be taught by a registered dietitian with experience in leading group-based behavioral weight loss interventions. Groups will meet weekly during weeks 0–13 and every 2 weeks during weeks 14–52. Weight will be obtained at each group meeting. Group sessions will last ~60 min and the curriculum will be delivered using a mix of large group discussion, small breakout discussions, visual demonstrations, and written exercises. Participants in the IMF group will be instructed in specific strategies to support IMF including strategies to deal with hunger on fast days, distraction techniques, and choosing a balanced diet/appropriate portions on fed days. Participants in the DCR group will be instructed in specific strategies to support DCR with a focus on daily calorie counting and food logging. Topics covered in both groups during the first 26 weeks include realistic weight loss goal setting, self-monitoring strategies, mindful eating, stress management, cognitive restructuring, improving personal food environments and social networks, and strategies to overcome barriers to healthy eating and increasing PA. Later in the curriculum (weeks 27–52), topics will focus on strategies for weight loss maintenance and include impact of weight loss on EE and propensity for weight regain, relapse prevention, and identifying motivation for long-term dietary and PA changes. Participants will also be provided two 10–15 min 1:1 phone calls with their group leader during the initial 26 weeks of the intervention for individualized dietary goal setting using a standardized protocol.

**Table 2 Tab2:** Weekly behavioral support topics covered in group-based sessions by randomized group

Study week^a^	General behavioral support topic	
	DCR	IMF
0	Introduction to DCR program	Introduction to IMF program
1	Getting started with DCR	Getting started with IMF
2	Portion control	Portion control
3	Food cues and meal planning	Food cues and meal planning
4	Food labels and macronutrient content	Food labels and macronutrient content
5	Wishes vs. reality/self-evaluation 1	Wishes vs. reality/self-evaluation 1
6	Moving those muscles	Moving those muscles
7	Stress management	Stress management
8	Exercise motivation, part 1	Exercise motivation, part 1
9	Dining out	Dining out
10	All about fats	All about fats
11	Mindful eating	Mindful eating
12	Environment	Environment
13	Exercise motivation, part 2	Exercise motivation, part 2
14	Recipe modifications	Recipe modifications
16	Exercise motivation, part 3	Exercise motivation, part 3
18	Cooking demo	Cooking demo
20	Motivation and self-evaluation 2	Motivation and self-evaluation 2
22	Special occasions/holidays	Special occasions/holidays
24	Volumetrics and fiber	Volumetrics and fiber
26	Guest speaker - licensed behavioral psychologist	Guest speaker - licensed behavioral psychologist
28	Boundaries	Boundaries
30	Breaking old habits and creating new ones	Breaking old habits and creating new ones
32	Behavior change identity	Behavior change identity
34	The energy gap	The energy gap
36	Situational and emotional eating	Situational and emotional eating
38	Lapse/relapse/collapse	Lapse/relapse/collapse
40	Fueling for exercise	Fueling for exercise
42	Weight plateaus	Weight plateaus
44	Self-talk	Self-talk
46	National Weight Control Registry	National Weight Control Registry
48	Micronutrients/supplements	Micronutrients/supplements
50	MythBusters	MythBusters
52	The future: ensuring you maintain your weight loss	The future: ensuring you maintain your weight loss

*DCR* daily caloric restriction, *IMF* intermittent fasting

^a^*Note*: These are the general sessions targeted; however, the actual timing of when these sessions will be taught may change based on holiday schedule and class cancelations due to weather

Behavioral support for PA will be provided within the weight loss program and will include discussion of health and weight benefits of PA, weekly PA goals to gradually achieve the target of 300 min/week moderate intensity PA, strategies to overcome barriers to PA, and strategies to improve exercise self-efficacy including exercise goal setting. Participants will also be provided a 20–30-min 1:1 in-person PA support session and a 10–15-min 1:1 follow-up telephone call with an exercise specialist during the initial 26 weeks of the intervention for individualized PA goal setting using a standardized protocol. IMF participants will be guided in strategies to adjust exercise duration on fast days (if needed) and still meet weekly PA targets. Participants will be provided access to the CU-AMC Anschutz Health and Wellness Center Fitness Center for the duration of the intervention.

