**Methods:**

The *D*aily Caloric *R*estriction vs. *I*ntermittent *F*asting *T*rial (DRIFT) is a two-arm, 52-week block randomized (1:1) clinical weight loss trial. The two intervention arms (DCR and IMF) are designed to prescribe an equivalent average weekly energy deficit from baseline weight maintenance energy requirements. Both DCR and IMF will be provided guideline-based behavioral support and a PA prescription. The primary outcome is change in body weight at 52 weeks. Secondary outcomes include changes in body composition (dual-energy x-ray absorptiometry (DXA)), metabolic parameters, total daily energy expenditure (TDEE, doubly labeled water (DLW)), EI (DLW intake-balance method, 7-day diet diaries), and patterns of physical activity (PA, activPAL device).

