### Sample size {14}

An a priori power calculation was performed for the primary outcome (weight) using nQuery 7.0 (Statistical Solutions Ltd, Cork, Ireland). In our power analyses, we made the following assumptions: (1) power ≥ 0.90 and above for the primary outcome is ideal; (2) the significance level under the null hypothesis will be set at *α* = 0.05; (3) null hypotheses will be tested against two-directional (that is, two-tailed) alternative hypotheses; (4) a 3-kg between-group difference in weight loss was deemed the minimum difference of clinical importance; and (5) the primary analysis will use the intent-to-treat principle in which all randomized participants are analyzed. We will enroll 150 participants (75 participants per randomized group) to provide 90% power at 5% significance to detect a between-group difference of 3 kg in body weight at 52 weeks. With an attrition rate of as high as 20%, we retain 82% power in a sensitivity (completer’s) analysis. Standard deviation (SD) of weight loss used in this calculation was 5.6 kg and was based on a 52-week interventional study using the Colorado Weigh program conducted at our research center [96]. There are no previous data for us to estimate the effect size for any of the outcomes at 52 weeks. If superiority of IMF to DCR cannot be established, we will perform a non-inferiority test using 2.26-kg weight loss as a non-inferiority margin. In this case, we would have 79% power to establish non-inferiority of IMF as compared to DCR assuming no difference in effect of weight loss between the two groups.

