#### Implementation {16c}

The study biostatistician will generate the allocation sequence. After all participants have completed screening and baseline assessments, participants will be notified of the randomization assignment on the first day of group class for the intervention. This process will take place separately within each cohort.

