### Statistical methods

#### Statistical methods for primary and secondary outcomes {20a}

Baseline characteristics will be summarized by treatment groups using descriptive statistics. Normality assumptions will be evaluated, and transformations used (e.g., square root and log) as appropriate. Body weight is the primary outcome variable and others are secondary or exploratory outcomes. Consequently, no adjustment for multiple outcomes will be applied. *P*-values < 0.05 will be considered significant. Any imbalance in baseline characteristics between groups that could potentially be a confounding factor for the outcome will be adjusted for in the statistical model.

The primary analysis will use the “intent-to-treat” principle and all randomized participants will be analyzed. Each continuous outcome will be analyzed using a linear mixed effects model. The fixed effects of the linear mixed effects model will consist of treatment group (IMF or DCR) and time of measurement (i.e., baseline and follow-up time points) and their interaction. Time of measurement will be treated as a continuous or categorical variable, as appropriate. Test of the interaction assesses the difference in post-intervention change from baseline between two groups and is used to quantify the effectiveness of the intervention. The 90% confidence interval for the interaction will be calculated. Incidence of adverse events, protocol modifications, and attrition will be compared between groups using chi square or Fisher’s exact test as appropriate.

To explore the impact of selected biologic, psychosocial, behavioral, and/or environmental variables on the intervention effect, we will initially apply models similar to those being tested in aim 1, with the addition of a potential effect moderator as a covariate and its interaction term (i.e., intervention × moderator × time interaction) in addition to related two-way interaction terms. Among factors with a significant three-level interaction, we will further use post-intervention weight loss as the outcome and multiple linear regression to examine their association with the outcome and its interaction with intervention. Similar multiple logistic regression analysis will also be conducted with the outcome dichotomized as responder and non-responder using clinical criteria.

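### Both diets are taught in arm-specific classes within cohorts, but the stated powers assume independent participants and no stated model term covers class

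*Protocol article*

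**What the plan says.** The Methods part of the abstract says that the trial "is a two-arm, 52-week block randomized (1:1) clinical weight loss trial". Sequence generation {16a} stratifies by sex only. Under Concealment mechanism {16b} and Implementation {16c}, allocation follows the baseline measures of a whole cohort: "This process will take place separately within each cohort".

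Under Group-based behavioral support, both arms receive a year of dietitian-taught group sessions that use large-group and breakout discussion, and "Randomized groups will meet separately". Each participant also has individual calls with the leader of his or her group.

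Sample size {14} plans 75 per arm "to provide 90% power at 5% significance to detect a between-group difference of 3 kg in body weight at 52 weeks". It also says "Standard deviation (SD) of weight loss used in this calculation was 5.6 kg". It adds 82% power for completers at 20% attrition, and 79% power for a fallback non-inferiority test with a 2.26 kg margin. It mentions no ICC, class size or design effect.

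Statistical methods {20a} states: "The fixed effects of the linear mixed effects model will consist of treatment group (IMF or DCR) and time of measurement", plus their interaction, with a 90% confidence interval for the interaction. The random effects are not listed. Section {20c} adds a sensitivity analysis of change scores by two-sample t-test or linear regression. Class and cohort appear in neither section.

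**The concern.** This is individual randomisation followed by group treatment, with clustering in both arms. Members of one class share peers, discussion and perhaps a leader for a year, so their weight changes may be more alike than those of people in different classes. Where that likeness belongs to a class in one arm, it adds to the variance of the difference between arms, and a calculation that counts 75 independent people per arm leaves it out.

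Two things are at stake. The first is the set of stated powers. The second is the validity of the superiority test and of the 90% interval that would carry the non-inferiority fallback. An interval that is too narrow makes it too easy to declare intermittent fasting superior or non-inferior.

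**Working it through.** **Inputs from the protocol article, Sample size {14}.** SD 5.6 kg, 75 per arm, difference 3 kg, two-sided 5%, attrition 20%, non-inferiority margin 2.26 kg. The 90% interval in {20a} corresponds to a one-sided 5% non-inferiority test.

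**Step 1: reproduce the stated powers with independent participants.**
- Standard error (SE) = 5.6 × √(2/75) = 0.914 kg. Superiority power = Φ(3/0.914 − 1.96) = 90.7% (90.3% by noncentral t). Stated: 90%.
- Completers, 60 per arm: SE = 5.6 × √(2/60) = 1.022 kg. Power = 83.5% (82.9% by noncentral t). Stated: 82%.
- Non-inferiority, 75 per arm, true difference zero: Φ(2.26/0.914 − 1.645) = 79.6% (79.3% by noncentral t). Stated: 79%.

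All three agree within two percentage points with a design effect of exactly 1, so no allowance for clustering was made.

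**Step 2: add class correlation.** The documents give neither the ICC nor the number of classes. Assumptions: 5 classes of m = 15 per arm, none of the class variance shared between arms, ICC 0.01 to 0.05.
- Design effect DE = 1 + (m − 1) × ICC
- True SE = 0.914 × √DE
- Two-sided type I error of a test that ignores class = 2 × [1 − Φ(1.96/√DE)]
- One-sided non-inferiority error = 1 − Φ(1.645/√DE)
- Power: as in step 1, with the true SE. The class-level version uses noncentral t on 2 × (5 − 1) = 8 df.

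| | ICC 0 | ICC 0.01 | ICC 0.02 | ICC 0.05 |
|---|---|---|---|---|
| DE | 1.00 | 1.14 | 1.28 | 1.70 |
| SE multiplier | 1.00 | 1.07 | 1.13 | 1.30 |
| Two-sided type I error, class ignored | 5% | 6.6% | 8.3% | 13.3% |
| One-sided non-inferiority error, class ignored | 5% | 6.2% | 7.3% | 10.4% |
| Superiority power, normal | 90.7% | 86.7% | 82.6% | 71.1% |
| Superiority power, 8 df | 82% | 77% | 72% | 60% |
| Non-inferiority power, normal | 79.6% | 74.9% | 70.5% | 59.9% |

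A simulation of the t-test that ignores class gave type I errors of 7.8% and 13.2% at ICC 0.02 and 0.05, in line with the formula.

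**Step 3: vary the number of classes, at ICC 0.05.**
- 3 classes of 25 per arm: DE 2.20, type I error 18.6%, superiority power 60%.
- 8 classes of about 9 per arm: DE 1.42, type I error 10.0%, superiority power 79%.

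**Step 4: vary how much class variance is shared.** Allocation is within cohort, so effects common to both arms of a cohort cancel. Simulated type I error at ICC 0.05 with 5 classes of 15 was 13.2% with none shared, 8.4% with half shared and 4.5% with all shared. The table in step 2 is the none-shared case.

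**Step 5: degrees of freedom if cohort is also a fixed effect.** With 5 cohorts and 10 classes, class-level df = 10 − 5 − 1 = 4 and the critical value rises from 2.31 (8 df) to 2.78. With the same SEs, superiority power is about 64% / 59% / 48% at ICC 0.01 / 0.02 / 0.05, and 69% even at ICC 0. Any shared cohort variance that the fixed effect removed would offset part of this loss.

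**The case against.** The strongest reply is that {20a} lists fixed effects only. A class term would normally be a random effect, random effects are often left to the statistical analysis plan, and that plan is not shown. This stands. A reader might infer that the primary analysis definitely treats participants as independent and that its error rates are inflated. The article does not support that; the inflation is conditional on no class random effect being fitted. The reply does not rescue Sample size {14}, where the stated powers hold only without clustering.

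A reader might also count every cohort or calendar influence as extra variance. That is not supported either: allocation is within cohort, so what both arms share cancels (step 4). The article does not say whether one dietitian leads both arms, so a leader effect may be partly shared too.

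The size is assumed, and parts of the design may keep the ICC low: matched session topics, individual calorie targets and one-to-one contacts. At ICC 0.01 the type I error is 6.6%, and at zero nothing changes.

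Taking the SD from an earlier study of the same programme is no answer. A total SD that includes class variance still needs the design effect in the SE.

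Finally, Trial status records enrolment as completed in April 2021. Restating power is therefore disclosure and cannot change the sample size. The analysis model is a separate matter: the article plans to submit the main results in 2023–2024.

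**Conclusion.** The point holds in conditional form. It is established that treatment is given in arm-specific classes within cohorts, that the stated powers assume independent participants, and that neither the stated model terms nor the t-test or regression sensitivity analysis contains class. It is not established that the final primary model omits class, or how large the ICC is.

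If class is omitted, any positive arm-specific correlation makes the week-52 interval too narrow. The error rates in step 2 rest on five classes of 15 per arm and no shared class variance; fewer classes make them worse, and more classes or shared variance make them milder. The powers in {14} are overstated for any positive arm-specific ICC, whatever model is used. The non-inferiority fallback matters most, because it rests directly on the width of the 90% interval.

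**What to change.** - Include in the primary model a random effect for class (cohort-by-arm) acting on change from baseline, with small-sample degrees of freedom such as Kenward-Roger or Satterthwaite. Use the same interval for superiority and non-inferiority, and carry the class term into the change-score sensitivity analysis.
- Do not make a cohort fixed effect compulsory. With few cohorts it uses up most of the class-level degrees of freedom (step 5).
- Report the number and size of classes and the estimated ICC.
- Restate superiority and non-inferiority power over a range of ICCs, for example 0.01 to 0.05, with the actual number of classes.

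The work is small: a paragraph of analysis text and one random term, and class membership should follow from cohort and arm. The statistical cost is a wider interval, fewer degrees of freedom and lower stated power. It may be substantial if classes are few: with 8 class-level df, superiority power is about 82% even at an ICC of zero.

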#### Procedures for monitoring adherence

Adherence to the prescribed dietary interventions for both randomized groups (DCR, IMF) will be monitored via (1) 7-day diet diaries, (2) monthly dietary adherence surveys, and (3) the DLW intake-balance method.

#### Criteria for discontinuing or modifying allocated interventions {11b}

Participants will not be withdrawn for non-adherence in this intent-to-treat study. Participants in both groups will be encouraged to adhere to the dietary prescriptions without modification for the initial 2 weeks as a prior study suggests individuals with obesity become habituated to IMF after ~2 weeks [38]. After the initial 2 weeks, a standardized dietary modification will be offered if a participant (1) expresses a desire to withdraw due to intolerance of study diet and/or (2) experiences adverse effects related to the study diet (i.e., insomnia, impaired concentration, headaches, irritability) that impair ability to function. DCR participants will be allowed to raise their calorie goal to target an energy deficit of 20% from weight maintenance requirements. IMF participants will be allowed to reduce fasting to 2 days per week (i.e., reduce targeted weekly energy deficit to ~20%). Participants will be allowed to continue these strategies for 2 weeks and will then be asked to re-try the original dietary prescription. If they are still unable to tolerate the original dietary prescription after a second attempt, they will be allowed to continue at the modified levels for the study duration. Percentage of participants in each group requiring sustained intervention modification will be recorded. The allocated interventions will not be modified other than as described above. However, participants may discontinue the intervention and/or choose to withdraw from the study at any time.

#### Relevant concomitant care permitted or prohibited during the trial {11d}

Participants will not be permitted to (1) engage in any other formal weight loss or exercise programs or clinical trials during the intervention, (2) use prescription or over-the-counter anti-obesity medications or supplements, and/or (3) undergo obesity treatment with bariatric surgery or endoscopic weight loss device placement.

#### Provisions for post-trial care {30}

Participants will not be provided any compensation if they experience harm or injury from participating in the study. Participants will continue to have access to the printed behavioral weight loss program materials that will be provided during the intervention after completion of study participation.

### Outcomes {12}

Participants will be asked to complete assessment visits at baseline and weeks 13, 26, 39, and 52 during the intervention as well as a follow-up assessment 26 weeks after completion of the 52-week study intervention (i.e., at week 78). See Table 3 for assessments by study timepoint. Body weight, measured in the clinic, is the primary study outcome. Among participants allocated to IMF, outcomes will be measured after a fed day.

**Table 3 Tab3:**
[figure not shown]
Schedule of enrollment, interventions, and assessments for the DRIFT study participants

*EI* energy intake, *REE* resting energy expenditure, *TDEE* total daily energy expenditure, *PAEE* physical activity energy expenditure, *PAL* physical activity level, *MVPA* moderate-to-vigorous physical activity

*All measures, post-allocation, will occur ±2 weeks from when the measure is due

**Screening measures include blood draw (complete blood count (CBC)), comprehensive metabolic panel (CMP), lipid profile, thyroid stimulating hormone (TSH), and hemoglobin A1C, electrocardiogram, height in centimeters (stadiometer), and physical exam and medical history

^#^Outcome weights will be taken in the morning, after an overnight fast, with the participant wearing a hospital gown. In the IMF group, weight will be taken in the morning following a fed day. Weight will also be measured weekly during weeks 0–26 and every other week during weeks 27–52 at the group-based behavioral weight loss sessions

^##^These measures will be collected monthly

^*†*^Outcome labs include glucose, insulin, triglycerides (TG), free fatty acids (FFA), beta-hydroxybutyrate (BHB), and cortisol. These will be measured at baseline after both a fed (i.e., 12-h fast) and fast day (i.e., 36-h fast, with exception of 25% EI). A lipid panel, insulin, glucose, hemoglobin A1C, leptin, ghrelin, peptide YY, highly sensitive C-reactive protein (hs-CRP), and brain-derived neurotrophic factor (BDNF) will be performed at baseline and weeks 26 and 52

^***††***^ Stored blood and stool samples will be collected at baseline and weeks 13, 26, 52, and 78 in subjects who consented to sample storage

^***†††***^See Table 4 for a detailed list of each construct for psychosocial, behavioral, and environmental factors

